### Implementation

Clusters of students will be randomly assigned (1:1) to either the intervention of control condiction by use of computer-generated randomisation list prepared by a research assistant independent from the research groups. The participants will be enrolled by principal investigator (XZ), with the assistance of head teachers.

### Blinding

Nether the participants nor the researchers will be blinded after assignment to the intervention.

## Methods: Data collection, management and analysis

### Data collection methods

Data relating to perceived stress, negative mental health outcome, positive mental health outcome and coping behaviours will be collected at baseline (T0=0 weeks), post-intervention (T1=12 weeks) and follow-up (T2=16 weeks). Demographic data will only be collected at baseline (see Table1 for study variables). All data will be collected online via the mobile intervention app.

Baseline variables, including demographics, will be gather at the start of the study (Table 1).

Table 2 Study variables

| **Variable** | **Measure** |
| --- | --- |
| Demographic | Age |
|  | Gender |
|  | Grade |
|  | Home location (rural or urban) |
|  | Guardian (parents or others) |
| Perceived stress | PSS-10 |
| Negative mental health | DASS-21 |
| Positive mental health | ORS-4 |
| Coping Behaviors | CISS-SFC |

A description of study instruments along with their reliability and validity are provided below:

The Perceived Stress Scale-10 Items (PSS-10) is a ten item self-reported scale to assess respondents’ global level of perceived stress (36). Respondents were required to rate the frequency of certain feelings they experienced over the past month on a 5-point Likert Scale (1=never, 2=rarely, 3=sometimes, 4=often, 5=always). It has shown to predict the range of health-related outcomes presumed to be associated with appraised stress (36). PSS-10 is a shorter version of Perceived Stress Scale 14-item (PSS-14) that assesses how respondents perceives their lives to be unpredictable, uncontrollable and overloaded (48). The PSS-10 has been validated in populations in different countries and proven to possesses adequate internal consistency with Cronbach’s alpha coefficients ranging from 0.67 to 0.91 (49-54), moderate convergent validity with stressful life events (55), and good concurrent validity with mental health problems such as anxiety and depression (56-58). Particularly, the PSS-10 has been translated in Chinese and shown acceptable reliability and validity in both adults (37, 38) and adolescents (39).

Negative mental health outcome (i.e., anxiety, depression and stress) will be measured using Depression, Anxiety and Stress Scale (DASS-21). DASS-21 consists of 21 items. Each item is rated on a 4 Likert scale ranging from 0 to 3, indicating to what degree each statement applied to participants over the past week. Summed scores range from 0-42 with more severe symptoms indicated by higher scores. This study will utilize total scores in addition to subscale scores. DASS-21 has been validated in Chinese adolescents and proved to have satisfactory psychometric properties in Chinese adolescent population (40).

Positive mental health status will be measured using Outcome rating scale (ORS). The ORS is a four-item self-report instrument. The ORS was developed as a brief alternative to the Outcome Questionnaire-45 (OQ-45)-a widely used and well-validated measure (41). The ORS was designed to assess change in three areas of client functioning generally considered valid indicators of treatment progress: individual (or symptomatic) functioning, interpersonal relationships, and social role performance (work adjustment, quality of life). The ORS was found to have adequate reliability and validity (42). The Chinese version of the ORS was recently validated in Chinese sample and showed to be a reliable and valid measure for Chinese sample and sub-clinical clients (43).

Stress coping behaviours will be measured using the short form of Coping Inventory for Stressful Situations (CISS-SFC). The CISS-SFC is a 21-item scale which measures three dimensions of coping-task-oriented coping, emotion-oriented coping, and avoidance-oriented coping. CISS-SFC has been translated into Chinese and approved to be satisfactorily valid and reliable among Chinese university students (44).

The usability and acceptance of the program will be assessed in order to gain information about users’ needs and specificities to improve interfaces of online programs for Chinese adolescents. Acceptance of the online program will be assessed by providing the users’ opportunity to write feedback at the end of each sessions. The contents of the written feedback of the online program will be evaluated. Usability will be assessed using measures such as the time they spent with the program and by the number of sessions they completed.

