## Objectives

This study aims to test whether an online school-based intervention for stress management is feasible, acceptable and effective among Chinese high school students. We hypothesise that our intervention (compared to the control group) will result in lower stress.

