### Interventions

The intervention group will download a stress-managing app, the app can be used on mobile devices including mobile phones and tablets etc. The app will be based on Stress Inoculation Training (SIT) developed by Meichenbaum (29). Even though SIT was designed for military settings, there has been a lot of studies which adapted the SIT and use it among students and adolescents (30-34) and delivered SIT via technologies (35). Our study will modify SIT to high school context by adding assertiveness and training participants cognitive and behavioural techniques to deal with stressors arising from academic environment and peer interpersonal relationships. The online stress-managing intervention will comprise of 11 sessions which consist of psychoeducation, problem assessments, training of stress coping skills (emotion-focused coping skills and problem-focused coping skills), cognitive restructuring, imagery and behavioural rehearsal and role play (see [Appendix 1](#_Appendix_1) for details of the intervention content). The intervention content will be in Chinese language. The control group will not be given access to the app until the termination of the trial (12 weeks after the start of the trial). There will be no other intervention given to the control group. Both the intervention group and the control group will have full access to usual care, which is the psychological courses arranged by the high schools.

The criteria for discontinuing for a given trial participant include: (i) if they self-reported or reported by others to be suicidal; (ii) if they drop out of school during the intervention period; (iii) if they require to withdraw from the study.

Strategies to improve adherence to intervention protocol include:

- Instructions about the importance of following study guidelines for adherence to once weekly product.
- Instructions about the purpose and use of the intervention app.
- Notification sent via app weekly on each Sunday that there will be a session taken in the app.
- Successfully completion of each session will generate a virtual star in the participant’s account as a reward for the participation.
- Adherence assessments include log in times and other usage data collected in the app.

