### Participant timeline

Table 1 and Figure 2 illustrate the time schedule of enrolment, randomization, interventions, and assessments for participants.

Table 1 Perceived Stress Reduction Protocol Schedule of Forms and Procedures

|  | | | **-1** | **T0** | **T1** | **T2** |
| --- | --- | --- | --- | --- | --- | --- |
| **Activity/**  **Assessment** | **Staff**  **Member** | **Approximate**  **Time to**  **Complete** | **Pre-Study**  **Screening/ Consent** | **Pre-Study**  **Baseline/**  **Randomization** | **Post-study**  **12 weeks** | **Follow-Up**  **16 weeks** |
| Consent Form | Head teachers | 20 Minutes | X |  |  |  |
| Inclusion/  Exclusion Form | Principal investigator | 5 minutes | X |  |  |  |
| Demographics Questionnaire | Principal investigator | 10 Minutes |  | X | X | X |
| PSS-10 | Principal investigator | 10 minutes |  | X | X | X |
| DASS-21 | Principal investigator | 20 minutes |  | X | X | X |
| ORS-4 | Principal investigator | 5 minutes |  | X | X | X |
| CISS-SFC | Principal investigator | 20 minutes |  | X | X | X |
| Randomization | Principal investigator | 15 Minutes |  | X |  |  |

[figure not shown]

Figure 2 Participant Timeline

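### Acceptability is an aim but is measured only by optional comments at the end of completed sessions, so the evidence leans towards students who persist and the app is likely to look more acceptable than it is

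*Protocol*

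**What the plan says.** The Objectives section names three aims together: that the intervention is "feasible, acceptable and effective among Chinese high school students".

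Acceptance has one assigned measure, in Data collection methods: "Acceptance of the online program will be assessed by providing the users’ opportunity to write feedback at the end of each sessions". The only stated use of the material is: "The contents of the written feedback of the online program will be evaluated". The same paragraph says that the purpose of assessing usability and acceptance is to learn about users' needs so that interfaces can be improved.

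Usage data are recorded but given other roles. For usability: "Usability will be assessed using measures such as the time they spent with the program and by the number of sessions they completed". For adherence, under Interventions: "Adherence assessments include log in times and other usage data collected in the app".

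Neither Table 1 (Participant timeline) nor Table 2 (study variables) lists an acceptability item at baseline, 12 weeks (T1) or 16 weeks (T2). Data collection methods also states that every item of data is gathered through the intervention app.

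**The concern.** Whether a student is asked for a view depends on the behaviour under judgement. A student who never completes a session has no occasion to comment. A student who stops partway can comment on the sessions finished, but is not asked about the one abandoned or the decision to stop. Comments on later sessions come only from those still using the app.

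The missing views matter for this aim. Recruitment says that both schools allow phones at weekends, and Interventions describes a Sunday prompt. Whether students fail to start or give up because of access, time, content or the interface bears directly on whether the programme is acceptable and workable in schools. No planned instrument collects those reasons.

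This is fixed at data collection. A later analysis plan can describe the comments received, but cannot recover answers that were never requested.

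**Working it through.** **No figure to reproduce.** The protocol states no acceptability rate, score, threshold or expected number of comments. Its sample size concerns efficacy only and is not affected.

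**Who is heard, by pattern of use**

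| Student allocated to the app | Asked for written feedback? | Asked why they did not start or stopped? | Usage record |
|---|---|---|---|
| Completes every session | After each session | Not applicable | Yes |
| Stops after k sessions | After sessions 1 to k only | No | Shows that use stopped, not why |
| Completes no session | Never | No | Shows no completed session, not why |

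**Illustration of direction and size.** Only the number of sessions comes from the protocol: "The online stress-managing intervention will comprise of 11 sessions". The other inputs are assumptions:

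- s = share of allocated students who stop early: 10%, 30% or 50%
- k = sessions finished by each stopper: 0, 3 or 6
- favourable view: 80% of finishers, 40% of stoppers
- one comment per completed session

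Formulas:

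- Share favourable among all allocated = (1 − s) × 0.80 + s × 0.40
- Share favourable among comments = [(1 − s) × 11 × 0.80 + s × k × 0.40] / [(1 − s) × 11 + s × k]
- Overstatement = second minus first

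Worked case, s = 0.30 and k = 3:

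- All allocated: 0.70 × 0.80 + 0.30 × 0.40 = 0.68
- Comments: (0.70 × 11 × 0.80 + 0.30 × 3 × 0.40) / (0.70 × 11 + 0.30 × 3) = 6.52 / 8.6 = 0.758
- Overstatement: 0.078, about 8 points

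| Share stopping | True share favourable | Overstatement, k = 0 | k = 3 | k = 6 |
|---|---|---|---|---|
| 10% | 76% | 4 points | 3 points | 2 points |
| 30% | 68% | 12 points | 8 points | 4 points |
| 50% | 60% | 20 points | 11 points | 6 points |

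**Sensitivity to the assumed views.** If stoppers and finishers are equally favourable, the overstatement is zero in every cell. If stoppers are more favourable (90%) and finish no session, the sign reverses. For s = 0.10 it is 0.80 − (0.90 × 0.80 + 0.10 × 0.90) = −0.01; for s = 0.30 and 0.50 it is −0.03 and −0.05. Acceptability is then understated by 1, 3 and 5 points.

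**Sensitivity to the number of sessions.** Appendix 1 lists a Session 12, against the 11 stated under Interventions. Using 12 changes no cell by as much as 1 point. The largest change is at s = 0.50, k = 6: (0.50 × 12 × 0.80 + 0.50 × 6 × 0.40) / (0.50 × 12 + 0.50 × 6) = 6.0 / 9 = 0.667, which is 6.7 points instead of 5.9.

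**The case against.** The case for the plan has four parts.

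First, feedback is offered after every session, so a student who leaves after session 5 has had five chances to comment. Views are captured before departure, which a single end-of-study form would not do. This stands. A reader might infer that students who stop say nothing at all; that is true only of those who finish no session.

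Second, disengagement is not hidden, because sessions completed, time spent and log-ins are recorded. This also stands, but those records show that a student stopped and not why, and the protocol assigns them to usability and adherence.

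Third, the written feedback is formative: no rate or threshold is planned, and no success definition under Outcomes involves acceptability. That lowers the stakes but does not remove the gap. The Objectives section still promises an answer on acceptability, and improving the interface also needs the views of those who gave up.

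Fourth, no stopping rate for app use is given. A reader might assume a steady loss of, say, 10–20% of remaining users at each session and conclude that last-session comments would come from a small minority. The documents offer no basis for such a rate. Their only attrition figure is the 10% drop-out allowance under Sample size, which would be 15 of 150 students per group. That allowance concerns leaving the study, and app disuse could exceed it, but by how much is unknown. Comments on a given session necessarily come from those who reached it, so a small number at the last session does not itself measure bias in overall acceptability.

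**Conclusion.** The point holds as a weakness in data collection for one stated aim. The single acceptability measure is optional free text tied to completing a session. Non-starters are unheard, and stoppers are neither heard after their last completed session nor asked why they left.

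The programme is likely to look more acceptable than it is. A reader might infer that this is certain, but the documents do not support that: the direction requires stoppers to be less favourable than finishers, which is plausible but not shown. On the assumed values above, the bias is small at 10% stopping (2 to 4 points) and material at 50% when stoppers finish few sessions (11 to 20 points). The protocol collects nothing that would show which case applies.

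The primary and secondary efficacy comparisons and the sample size are not affected. The change is worth making before data collection because it is cheap and the information cannot be obtained afterwards by analysis.

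**What to change.** Add to the existing 12-week assessment, for every student allocated to the app whether or not they used it, a few rated acceptability items and one question on the reason for not starting or for stopping. Enter these in Tables 1 and 2.

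Because all data are to be collected in the app, offer these items by a route that does not depend on continued app use, such as a web link. Report the 12-week response among students who stopped.

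Keep the end-of-session comments as supplementary evidence. Report them beside sessions completed and the number commenting at each session, out of all students allocated to the app.

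The cost is a few minutes for intervention students at an assessment that already exists, plus setting up the alternative route; no visit is added. Response from students who left will still be incomplete, so the change reduces the gap without closing it.

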### Data management

In the intervention, all data will be entered electronically. This will be done at the participating site where the principal researcher (XZ) will be located during the intervention period. To ensure the security of the data, originally data will be re-entered to Microsoft Word documents and stored on the UQRDM, the cloud data management system owned by the sponsor of this trial (The University of Queensland).

### Statistical methods

Statistical analyses will be performed using SPSS 22.0 (SPSS Inc., Chicago, IL). We will present descriptive data in a table: categorical variables (e.g., gender, grade, home location etc.) will be presented as counts and percentages. Continuous variables (e.g., age, PSS-10, DASS-21, ORS-4 etc.) will be presented as mean and standard deviation (SD).

To determine whether any significant differences exist between intervention group and control group at baseline, independent t test will be conducted on continuous baseline variables (e.g., age, PSS-10, DASS-21, ORS-4, CISS-SFC, MER), and chi-square analyses will be conducted on categorical or nominal variables (e.g., gender, home location, guardian etc.).

To determine whether the intervention is effective, intention-to-treat (ITT) analyses will be conducted separately (59). The ITT analysis will include the data from the whole randomized sample. A linear mixed model (LMM) will be used to investigate the effects of time and groups on the primary outcome variables. The LMM will be performed with group, time, and group × time as fixed effects. Subjects and schools will be selected as random effects in order to take into consideration both within-subject and within-school correlations. Cohen d effect sizes will be calculated to examine the magnitude of between-group differences. Similar analyses will be conducted for exploring effects on secondary outcome measures.

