## Trial design

A superiority, two-arm, cluster randomized controlled trial will be conducted (see Figure 1 for the flow chart of the trial design). Confirmed participants will be randomly allocated in a 1:1 ratio into one of the study groups. In the intervention group, the participants will use an online stress-managing program which will be delivered via smartphone. Participants in the control group will not use the online program duration. However, they will be notified that they will have access to the online program after 12 weeks (i.e., at the end of the study). The condition to which each participant will be allocated will not be blinded for either experimenters or participants.

[figure not shown]

Figure 1 Flow chat of the trial design

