### Sample size

According to a meta-analysis on internet interventions on stress reduction (45), which reported that the overall mean effect size for stress at posttest was Cohen d=0.43 (95% CI 0.31-0.54). Significant, small effects were found for depression (Cohen d=0.34, 95% CI 0.21-0.48) and anxiety (Cohen d=0.32, 95% CI 0.17-0.47). Following this meta-analysis, we therefore choose effect sizes of d=0.43 for perceived stress, d=0.34 for depression and d=0.32 for anxiety. An absolutely reduction of 4.03 points is chosen as minimum clinically significant difference according to a previous study that analyzed PSS-10 scores in terms of minimum clinically significant important difference (MCID) (46). Based on this expected difference, no expected PSS-10 change in the control group, a population mean PSS-10 of 13.7 (SD=5.6) equal between groups (47), a sample size of 172 (n=86 in each study group) is required to detect effect size of d=0.43 with a power (1− β) of 0.80 with alpha of 0.05. A sample size of 192 (n=96 in each study group) will be needed when allowing for 10% drop out. Considering the availability of target sample, we will choose a sample size of 300 (n=150 for each study group).

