## Assignment of interventions

### Allocation

A two-arm randomized controlled trial will be conducted. Confirmed participants will be randomly allocated in a 1:1 ratio into one of the study groups. Students will be randomised within schools. In order to minimise contamination, students will be randomised on a class basis. Also, students will be notified that all of the participantas will have access to the online program, therefore they should not talk to each other about the content of the intervention. In the intervention group, the participants will use an online stress-managing program which will be delivered via smartphone. Participants in the control group will not use the online program duration. However, they will be notified that they will have access to the online program after 16 weeks (i.e., at the end of the study). The condition to which each participant will be allocated will not be blinded for either experimenters or participants.

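### The baseline t and chi-square tests treat students as independent although classes are randomised, so their p values are too small; how much too small depends on a class size and ICC that the protocol does not give.

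*Protocol*

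**What the plan says.** The design is clustered. Trial design states: "A superiority, two-arm, cluster randomized controlled trial will be conducted". Allocation names the unit: "In order to minimise contamination, students will be randomised on a class basis", and adds that this is done within schools. Implementation repeats that clusters are assigned 1:1.

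Statistical methods gives the purpose of the baseline tests: "To determine whether any significant differences exist between intervention group and control group at baseline". For this, "independent t test will be conducted on continuous baseline variables" (age and the outcome scales are among those listed) and "chi-square analyses will be conducted on categorical or nominal variables" (gender, home location and guardian are named). Neither test has a term for class. The same section already plans descriptive tables of means with SDs and of counts with percentages. It attaches no rule to the result of the baseline tests.

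For the efficacy model, "Subjects and schools will be selected as random effects"; the fixed effects are group, time and their interaction.

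**The concern.** An independent t test or a Pearson chi-square test takes each student as a separate randomised unit. Here whole classes move together. If classmates resemble each other, the difference between arms varies more than these tests allow for, and their p values are too small.

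The tests also answer a question of little use. Where baseline is recorded before allocation, any difference between arms arises by chance, and a p value does not show whether an imbalance is large enough to matter for the PSS-10.

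At stake is the credibility of the baseline table. A reader who sees significant differences may doubt a sound randomisation when the tests themselves are too liberal.

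**Working it through.** **Inputs from the protocol.** Class is the unit of randomisation (Allocation). The planned total is 300, with 150 per arm (Sample size). The two schools have more than 2000 and more than 3500 students in grades 10 and 11, and participants are volunteers who identify themselves as stressed (Recruitment). The 5% level is taken from Sample size; no level is stated for the baseline tests.

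**Inputs assumed.** Participants per class (m), the ICC and a class size of 50. The protocol gives none of these.

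**The plan's own figure.** The protocol states no error rate for the baseline tests. The figure it does state is the sample size, which "is required to detect effect size of d=0.43 with a power (1− β) of 0.80 with alpha of 0.05". For two independent groups, n per arm = 2(1.96 + 0.84)²/0.43² = 85, or 85.87 with the t distribution, so 86 per arm and 172 in total. For 10% dropout, 86/0.9 = 95.6, so 96 per arm and 192 in total. Both figures reproduce, and both treat students as independent.

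**Error rate of a test that ignores class.**

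- Design effect: DE = 1 + (m − 1) × ICC.
- Actual rate of a nominal 5% two-sided test: 2 × [1 − Φ(1.96/√DE)].
- Lower example: m = 10, ICC = 0.05. DE = 1 + 9 × 0.05 = 1.45; 1.96/√1.45 = 1.63; rate 10.4%.
- Upper example: m = 30, ICC = 0.10. DE = 1 + 29 × 0.10 = 3.90; 1.96/√3.90 = 0.99; rate 32.1%.

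| Participants per class | ICC 0.01 | ICC 0.05 | ICC 0.10 |
|---|---|---|---|
| 2.7 | 5.2% | 6.0% | 7.0% |
| 10 | 6.0% | 10.4% | 15.5% |
| 25 | 7.8% | 18.6% | 28.8% |
| 30 | 8.4% | 21.1% | 32.1% |

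The first row is the case of volunteers spread over all classes: 5500/50 = 110 classes, and 300/110 = 2.7 per class.

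**Check by simulation.** In 4000 trials per setting, with about 300 students, whole classes randomised and no true difference, the student-level t test rejected in 10.2% (m = 10, ICC 0.05) and 32.0% (m = 30, ICC 0.10), in line with the formula. For a binary variable, with the ICC on the latent scale, the chi-square test rejected in 10% to 25% over m = 10 to 30 and ICC 0.05 to 0.10. A t test on class means stayed between 4.3% and 6.0% in every setting (m = 5 to 50, ICC 0 to 0.20).

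**Grade-linked variables.** Age should cluster strongly if each class belongs to one grade. At an assumed ICC of 0.3 to 0.5, the formula gives 11% to 15% at 2.7 per class, 31% to 40% at 10 per class and 53% to 62% at 30 per class.

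**The case against.** The main objection concerns size, and it stands. A reader might infer that significant imbalances will appear far more often than 5%, or that the trial will probably report a failed randomisation. The protocol does not support either statement. Nothing confines the 300 volunteers to a few classes, and with few per class most variables stay at 5% to 7%.

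A reader might also combine the variables. For five independent ones at 10.4% to 32.1% each, 1 − (1 − p)^5 gives 42% to 86%, against 1 − 0.95^5 = 23% at a true 5%. But most of the continuous variables are self-reported stress, mental-health or coping scales from the same students. Independence is implausible, so no such figure should be relied on.

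A third inference is that covariates will be picked from the significant results. The protocol contains no selection step, and the fixed effects of the model are already named. The baseline tests alter neither the primary estimate nor its p value.

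Nor can one say that every baseline difference must be due to chance. Table 1 puts baseline and randomisation in one column without stating their order, Appendix 1 places assessments within intervention Session 1, and allocation is unblinded. Answers given after allocation could differ for other reasons.

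Finally, a separate analysis plan may add detail. That does not remove the point: the protocol itself names these tests, and as named they do not match its design.

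**Conclusion.** The mismatch is real. For any positive ICC with more than one participant per class, the planned tests reject too often. The size is conditional: about 10% to 32% for the t test if 10 to 30 participants come from each class and the ICC is 0.05 to 0.10; about 5% to 7% if volunteers are spread at about 2.7 per class with ICC 0.01 to 0.10; higher for variables tied to grade. All of these rest on assumed class sizes and ICCs.

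The consequence is limited to misleading evidence of imbalance in the report, so this is a minor point that is worth fixing because it is cheap. The absence of class from the efficacy model is a separate issue and matters more.

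**What to change.** - Delete the baseline significance tests. Describe balance by arm with means and SDs or counts and percentages, add standardised differences, and report the number of classes per arm. If a test is kept, use class means or a mixed model with class as a random effect.
- State in advance that the outcome model adjusts for the baseline value of the outcome, in one of two ways: as a covariate with only T1 and T2 as responses, or with T0 kept as a response and the arm means constrained equal at baseline. Doing both would use the baseline score twice.
- Because both options rely on baseline being recorded before allocation is known, state that order.
- Enter school as a fixed effect in place of the random effect, which has only two levels.

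The cost is one rewritten paragraph in Statistical methods. No new data are needed, since the baseline scores are already collected and the descriptive table is already planned.
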